## Abstract

**Introduction:**

Digital health measures promise to further improve the quality of cardiovascular care but have not yet been widely implemented in routine care. The research project Digital preventive measures for arterial hypertension (DiPaH) will systematically identify structural and individual factors in different stakeholders that influence the use of digital preventive measures in patients with arterial hypertension in Germany. Special focus is given to remote and sparsely populated areas, the age-specific impact, as well as influence of digital health literacy.

**Methods and analysis:**

The DiPaH project is an exploratory cross-sectional study with a mixed-methods design, in which written surveys and interviews with patients and physicians will be conducted. In addition, secondary data from a health insurance company will be analyzed. In module 1, individuals from the database of the health insurance company with confirmed arterial hypertension will be interviewed (1,600 questionnaires, 30 interviews). Module 2 includes users of digital prevention offers and apps (400 questionnaires, 40 interviews) and in module 3, family physicians and cardiologists will be interviewed (400 questionnaires, 40 interviews). In a final module, the overall results will be analyzed and recommendations for interventions in clinical care will be derived.

**Discussion:**

The DiPaH project will contribute to a patient-oriented and demand-based improvement of arterial hypertension prevention services in health care. Challenges and barriers will be analyzed and the respective target groups identified based on their prevention needs and social characteristics to enable a patient-centered implementation of digital prevention of arterial hypertension and cardiovascular services in general, and finally to improve cardiovascular outcomes.

**Clinical trial registration:**

https://drks.de/search/de/trial/DRKS00029761, identifier DRKS00029761.

## Introduction

Despite effective guideline-based prevention and treatment options, cardiovascular diseases remain the leading cause of death worldwide (1). Arterial hypertension is one of the most important risk factors for cardiovascular diseases (2), affecting over one billion people worldwide (3). In addition to a genetic predisposition, the development of hypertension is strongly influenced by individual factors such as lifestyle (4), but also by local access to and quality of health care (5). In Germany, the prevalence of such risk factors varies greatly depending on the region. For example, obesity is more prevalent in the rural federal states (6). But it is precisely there that accessibility to medical care is limited due to a low density of doctors (7). As a result, hypertension-related diseases such as ischemic heart disease are most frequent in these states (8). On an individual level, there is also an association between hypertension and lower socioeconomic status and lower educational attainment (9). In summary, there are significant regional differences in Germany, with a higher incidence of arterial hypertension in socioeconomically disadvantaged areas (10).

In order to overcome these geographical disparities in health care and to strengthen individual health behavior even in regions with poor access to health care and aging population, digital prevention measures are an innovative and promising approach (11). These are digital applications such as remote monitoring (i.e., telemonitoring), e-learning, or m-health apps. The characteristics of digital preventive measures for arterial hypertension are shown in Figure 1. With telemonitoring, patient data is transmitted to the attending physicians (12). E-learning provides patients with information, e.g., on lifestyle modification through interactive and web-based educational material (12), and m-health apps are stand-alone software on a smartphone or tablet (13). Despite existing technical possibilities, digital health applications have so far only been insufficiently implemented (11), so that there is an increasing risk of a “digital divide” (14), whereby vulnerable groups with low digital health literacy are progressively excluded from innovative health offers. Current data (15) from Germany show low mobile Internet use among older people (only 36% of the population born up to 1945) and among people with lower educational attainment. Importantly, usage is lower in the more rural eastern German states than in the western states. Since people with lower incomes have less access to digital devices (15), one cause could be the lower gross average income in eastern Germany (16). However, people who are more limited in their mobility and have a higher risk of illness could particularly benefit from digital measures. Importantly, data on hypertension-specific digital applications are lacking so far.

**FIGURE 1 F1:**
[figure not shown]
Characteristics of digital preventive measures for arterial hypertension.

Due to the importance of digital health interventions, the ESC e-Cardiology Working Group has published a position paper in 2019 addressing the challenges of digital health adoption in cardiovascular medicine (11). In addition to technical issues, there are also patient- and physician-related barriers [e.g., lack of information about available and qualified m-health apps (17), lack of digital skills (15)] as well as reimbursement and legal considerations to the introduction of digital health in cardiovascular medicine that need to be carefully analyzed and addressed prior to their successful deployment.

To overcome such barriers, the healthcare research project digital preventive measures for arterial hypertension (DiPaH) will therefore systematically identify individual, structural and application-related factors that influence the use of digital preventive measures in patients with arterial hypertension in Germany. Due to the regional differences already described, a particular focus of the study is on remote and sparsely populated areas, the age-specific effects as well as the influence of digital health literacy.

The study identifies not only general barriers to the use of digital prevention services, but also barriers specific to patient groups (e.g., with regard to motivation and health literacy). In order to take into account the complexity of prevention in statutory health insurance, the DiPaH study relates the experiences of patients and users of digital applications to the perspective of physicians. In this way, potentials, but also barriers that only emerge in the overall context of the health care system, can be identified and corresponding concrete recommendations for implementation can be derived.

This study protocol presents the study design for each subgroup and describes the study population, the methodological approach (including data collection and data analysis), the relevant outcomes and the quality criteria of the study, and discusses the expected benefits and limitations. The aim is to give an overview of the different sub-studies (modules), to describe contexts and to present the methodological approach.

## Methods and analysis

### Design and setting of the study

The mixed-methods study will be conducted in multiple phases. Quantitative and qualitative methods will be performed in a parallel or in a sequential order (18). Standardized surveys are used to obtain a representative and comprehensive understanding of the different stakeholder groups and to make the answers comparable. The qualitative methods are suitable to contextualize and interpret the data appropriately (18). The methodological openness of qualitative methods also allows aspects to be included that arise from everyday conditions and are accordingly not yet theoretically accessible at the beginning of the study, for example organizational barriers in everyday practice (19). Methodological triangulation allows the results of quantitative and qualitative interviews to be validated against each other (20).

Figure 2 shows a summary of the study design, methods and the main focus of interest in each module. Since the focus is on the user perspective, we will include patients with arterial hypertension, users of digital health services and physicians. The timeline of recruitment is presented in Table 1.

**FIGURE 2 F2:**
[figure not shown]
Study design.

**TABLE 1 T1:** Dates of recruitment.

Substudy	Dates of recruitment
Module 1 interviews	Q3 2022 – Q1 2023 (6 months)
Module 1 questionnaires	Q4 2023 – Q1 2024 (4 months)
Module 2a interviews and questionnaires	Q4 2022 – Q3 2023 (11 months)
Module 2b interviews and questionnaires	Q4 2022 – Q3 2023 (11 months)
Module 3a interviews	Q4 2022 – Q2 2023 (5 months)
Module 3a questionnaires	Q4 2023 – Q1 2024 (4 months)
Module 3b interviews	Q4 2022 – Q2 2023 (5 months)
Module 3b questionnaires	Q4 2023 – Q1 2024 (4 months)

Q, quarter. Q1 = Jan–Mar, Q2 = Apr–Jun, Q3 = Jul–Sep, Q4 = Oct–Dec.

The study will be conducted in Germany with a regional focus on the metropolitan area of Berlin and the rural, sparsely populated federal states of Brandenburg and Mecklenburg-Western Pomerania.

### Selection of subjects

The sub-study specific inclusion criteria are summarized in Table 2. Exclusion criteria are age under 18, lack of consent and considerable limitations to speak and understand German fluently.

**TABLE 2 T2:** Additional inclusion criteria.

Substudy	Inclusion criteria
Module 1 interviews	Diagnosis of arterial hypertension
Module 1 questionnaires	Diagnosis of arterial hypertension and health-insured by the AOK Nordost
Module 2a	Participation in a behavioral prevention course offered by AOK Nordost
Module 2b	Use of a hypertension app within the last 2 years
Module 3a	Current work as a family physician
Module 3b	Current work as a specialist in cardiology

In module 1, insured persons of the statutory health insurance company AOK Nordost with arterial hypertension will be surveyed on preferences and barriers to the use of (digital) prevention measures (*n* = 1,600 questionnaires). Questionnaire data will be linked to routine data to analyze further health-related factors. Prior to the AOK Nordost survey, a preparatory qualitative interview study will be conducted with hypertension patients recruited through clinics and practices (*n* = 30).

In module 2a, users of (digital) prevention services offered by AOK Nordost will be surveyed on their motivation to participate in the interventions, the advantages and disadvantages of digital vs. analog measures, and possible barriers to the services (*n* = 200 questionnaires, *n* = 20 interviews).

In module 2b, users of the hypertension-specific app “Hypertonie.App” (21) will be interviewed about their motivation for using the app, about possible restraining factors when using a hypertension app and how they became aware of the app (*n* = 200 questionnaires, *n* = 20 interviews). The app includes features for documenting blood pressure, personalized health information, breathing exercises, and reminder functions.

In module 3, family physicians (3a) and cardiologists (3b) will be surveyed on their attitudes toward digital health applications, structural and individual barriers, and information needs in medical practice (*n* = 400 questionnaires, *n* = 40 interviews).

### Sample size calculation

A sample number of *n* = 200 is required per subgroup. The sample number is calculated according to an *a priori* power analysis (G*Power) for the χ^2^ test for dichotomous variables with the following assumptions: moderate effect (*w* = 0.2), α = 0.05, power (1-β) = 0.80, Df = 1 (required sample size *n* = 197).

In Module 1, eight subgroups will be identified by age, gender, and rural vs. urban residence (per subgroup *n* = 200, total *n* = 1,600).

### Outcomes

The DiPaH study will collect data through questionnaires and interviews on a one-time basis. The relevant outcomes are digital health literacy [eHEALS (22, 23)], health literacy [HLS-EU-Q6 (24, 25)], motivation action stage [HAPA Assessment (26, 27)], self-concept related to information and communication technology (28), perception of usability [System Usability Scale (29, 30)], guideline-adherent medication (4), adherence [MMAS-8D (31, 32)]. The outcomes and measurement tools are presented in Table 3. In addition, the following outcomes will be explored in all modules: attitudes toward digital prevention, use of digital prevention, motivation to use digital prevention, barriers to digital prevention, perceived advantages and disadvantages of digital prevention, information needs, and – just for patients – pathways to health care. For these outcomes, module-specific items will be developed and piloted by the research team. In addition, these themes will be explored in greater detail in the qualitative interviews.

**TABLE 3 T3:** Outcomes and measurement tools.

Outcome	Measurement tools	References	Items	Reliability	Module				
					1	2a	2b	3a	3b
Digital health literacy	eHEALS	Norman and Skinner (22), German: Soellner et al. (23)	8	Cronbach’s α = 0.828 to Cronbach’s α = 0.877	x	x	x		
Health literacy	HLS-EU-Q6	Sørensen et al. (24), Short Version: Pelikan et al. (25)	6	Cronbach’s α = 0,803	x	x			
Motivation action stage	HAPA Assessment: stage assessment	Lippke et al. (27)	1	Sensitivity = 70% to 80% Specificity = 80% to 87%	x		x		
Self-concept related to information and communication technology	General ICT-SC	Schauffel et al. (28)	5	Cronbach’s α = 0.95	x	x			
Perception of usability	System Usability Scale	Brooke (30), Bangor et al. (29)	10	Cronbach’s α = 0.911			x		
Adherence	MMAS-8	Morisky et al. (32), German: Arnet et al. (31)	8	Cronbach’s α = 0.41	x				
Guideline-adherent medication	ESC guideline criteria	Williams et al. (4)			x				

Input variables in all modules will be sociodemographic characteristics of patients (age, gender, rural vs. urban residence, federal state, education, income) and physicians (age, gender, rural vs. urban location of medical practice, federal state, experience). In Modules 1 and 2b, health-related characteristics will be collected in more detail (current medication, disease status, comorbidities). In Module 2a, the interactivity of the course is additionally assessed as an input variable.

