### Statistical analyses

First, the data from the standardized questionnaires will be presented descriptively (absolute and relative frequency, median and standard deviation). In further steps, correlation analyses will be performed. The correlation between two binary variables is analyzed with the χ2-test. For continuous outcome variables and binary influence factors, *t*-tests will be performed and means and 95% confidence intervals will be reported. Regression analyses will be performed to analyze possible associations between patient characteristics (such as sociodemographic variables) and outcomes of interest (e.g., digital health literacy).

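### Module 2a: if interactivity is a fixed course attribute and several respondents share a course, the named chi-square and t-tests would give p-values and confidence intervals that are too optimistic

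*Protocol article*

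**What the plan says.** The Outcomes section of the protocol article lists sociodemographic input variables for all modules and then adds one that is specific to this sub-study: "In Module 2a, the interactivity of the course is additionally assessed as an input variable". Table 2 (Selection of subjects) gives the Module 2a entry criterion as "Participation in a behavioral prevention course offered by AOK Nordost". The same section plans 200 questionnaires for the module.

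Under Statistical analyses, the rule for two binary variables is "The correlation between two binary variables is analyzed with the χ2-test". For a binary factor and a continuous outcome it is "For continuous outcome variables and binary influence factors, *t*-tests will be performed and means and 95% confidence intervals will be reported". Regression is also planned for patient characteristics, but neither the model type nor the error structure is stated.

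Under Sample size calculation, "A sample number of *n* = 200 is required per subgroup". This rests on a chi-square test with w = 0.2 and "α = 0.05, power (1-β) = 0.80, Df = 1", which gives 197.

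The article does not say how many courses there are or how many respondents share one. It also does not say whether interactivity is a property assigned to the course or a rating by the respondent, or whether it is binary.

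**The concern.** Respondents enter Module 2a because they took a course from one insurer's offer. On its plain wording, interactivity describes the course. If so, it has one value for everybody who took the same course, and whatever else those people share (content, trainer, type of audience) cannot be separated from it by counting respondents. The information on a course-level factor then lies somewhere between the number of courses and the number of respondents. The chi-square test, the t-test and a plain regression on respondents all use the number of respondents.

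At stake is that a difference between a few particular courses could be reported as an association with interactivity, with an interval that is too narrow. The Discussion says the results will feed recommendations to service providers and health insurers.

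Timing matters too. Under Data capture and storage, Module 2a uses a mailed questionnaire with an online option, contact details are held apart from the research data, and linkage to insurer data is described for Module 1 only. Unless the course is captured with the response, a later analysis plan may have no means of accounting for it.

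**Working it through.** **Inputs from the article:** 200 Module 2a questionnaires; w = 0.2, alpha 0.05, power 0.80, 1 degree of freedom; stated n = 197.

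**Assumed, because the article does not give them:** respondents per course (m) from 1 to 20; ICC 0.01, 0.05 and 0.10; courses of equal size, half of them interactive.

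**Step 1: the plan's own figure.** By the normal approximation, n = ((1.960 + 0.842)/0.2)² = 196.2, so 197. With the noncentral chi-square (noncentrality n × w²), power is 80.2% at n = 197 and 80.7% at n = 200. The stated figure is reproduced for independent respondents.

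**Step 2: a factor that is constant within courses.** The design effect is DE = 1 + (m − 1) × ICC. The actual type I error of a test that ignores courses is 2 × [1 − Φ(1.96/√DE)].

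Example with m = 20 (10 courses) and ICC 0.05: DE = 1 + 19 × 0.05 = 1.95; √1.95 = 1.396; 1.96/1.396 = 1.404; type I error about 16.1%. The effective sample is 200/1.95 = about 103, and a correct interval is about 40% wider than the naive one.

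Actual type I error at nominal 5%:

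| Respondents per course | ICC 0.01 | ICC 0.05 | ICC 0.10 |
|---|---|---|---|
| 1 | 5.0% | 5.0% | 5.0% |
| 2 | 5.1% | 5.6% | 6.2% |
| 5 | 5.5% | 7.4% | 9.8% |
| 10 | 6.1% | 10.4% | 15.5% |
| 20 | 7.2% | 16.1% | 25.0% |

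**Step 3: check by simulation.** With 10,000 simulated t-tests per scenario, the type I error was 10.9% (m = 10, ICC 0.05), 15.7% (m = 20, ICC 0.05) and 25.1% (m = 20, ICC 0.10). It was 4.8% to 5.2% at m = 1 with a positive ICC. This agrees with the formula.

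**Step 4: interactivity as a respondent rating.** When half of each course was placed in each group, so that the factor varied within courses, the simulated type I error was about 4% to 5%. There is no inflation in this case.

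**Step 5: what n = 200 means for a course-level factor.** The number needed for 80% power is 197 × DE. At ICC 0.05 this is 237 for m = 5 (DE 1.20), 286 for m = 10 (DE 1.45) and 385 for m = 20 (DE 1.95). A t-test on course means held about 5% in simulation at ICC 0.05. Its power at w = 0.2 was 44% with 10 courses, 61% with 20 and 73% with 40.

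**The case against.** The strongest case against is that the inflation needs three conditions, and the article states none of them: several respondents per course, a positive ICC, and interactivity that is constant within a course. Data in this study come from questionnaires and interviews, so a rating by each participant is a natural reading, and for freely varying ratings Step 4 shows no inflation. The questionnaires go to insured persons, and no sampling by course is described, so there may be few respondents per course. This stands, and it is why the point is conditional.

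The article also does not tie interactivity to the chi-square or t-test. It does not call the variable binary, and the unspecified regression could carry a course effect. Handling of clustering is commonly left to an analysis plan or full protocol, neither of which is shown. This stands as well: the silence is not in itself an error. What remains is that the only tests named assume independence, that one listed factor is worded as a course property, and that the identifier needed for a remedy has to be collected with the data.

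Three stronger readings are tempting, and the article does not support them:

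- A reader might infer that the interactivity comparison is certain to produce too many false positives. At 2 respondents per course the error is at most about 6% for an ICC up to 0.10.
- A reader might extend the point to a comparison of digital with analog courses. In Module 2a, digital versus analog is a topic on which participants give their views. It is not a listed input variable, and no test of it is planned.
- A reader might infer that 80% power was promised for interactivity. The calculation is a generic one per subgroup and makes no such promise.

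**Conclusion.** The point holds in conditional form. If interactivity is a fixed course attribute and courses are shared by several respondents, plain chi-square and t-tests would give p-values and 95% confidence intervals that are too optimistic for this one factor. Over an assumed ICC of 0.01 to 0.10 the effect is small at 2 respondents per course and substantial at 10 to 20. The ICC and course sizes are assumptions throughout. The n = 197 calculation is correct for respondent-level factors such as age, gender, residence and education. It does not carry over to a course-level factor. Severity is low: the study is exploratory, interactivity is one additional input variable in one sub-study, and no confirmatory hypothesis depends on it.

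**What to change.** 1. Record the course (title or provider, and group where there is one) with each Module 2a response.
2. State whether interactivity is assigned to the course or rated by the respondent.
3. Report the number of courses, overall and per level of interactivity, and the number of respondents per course.
4. Where courses are shared, analyse interactivity with a linear or logistic mixed model with a random intercept for course, in place of a plain chi-square or t-test. With few courses, use a small-sample correction or compare course means.
5. Add a sentence that the n = 200 calculation applies to respondent-level factors and not to a course-level factor.

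The cost is one extra identifier and a few sentences of text, with no additional respondents. The downside is wider intervals and lower stated power for interactivity where courses are shared. If nearly every respondent turns out to come from a different course, the results will hardly change.

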### Statistical analyses

First, the data from the standardized questionnaires will be presented descriptively (absolute and relative frequency, median and standard deviation). In further steps, correlation analyses will be performed. The correlation between two binary variables is analyzed with the χ2-test. For continuous outcome variables and binary influence factors, *t*-tests will be performed and means and 95% confidence intervals will be reported. Regression analyses will be performed to analyze possible associations between patient characteristics (such as sociodemographic variables) and outcomes of interest (e.g., digital health literacy).

